#### Participant recruitment

Participants will be recruited in health care facilities in Germany. For this purpose, the health insurance companies contact the executives of their collaborating hospitals, stationary elderly care facilities, and ambulatory care providers. The executives will forward an explanatory video to their employees via in-house communication networks, whereupon they can voluntarily enter their contact details into an online tool to register for the study. Previous experiences of the researchers showed that approximately only half of all contacted nurses participated in intervention studies. Therefore, in order to reach the target sample size, we will contact double the participants than we will actually include in the study.

### Interventions

#### Explanation for the choice of comparators

In order to illustrate the advantages of mHealth interventions for the specific requirements of healthcare settings, office workers were chosen as a comparison group. The reason for choosing this comparison group is that office workers are often more likely to adapt to digital interventions due to their workplaces being better equipped in terms of technology. In addition, as described above, we developed five different study scenarios to be compared within the study. The reason for this selection is to reflect different levels of individualization in mHealth interventions across the different scenarios.

#### Intervention description

As described above, there are five different intervention scenarios, each including a WBT or an app, and each with different levels of individualization. This trial becomes particularly complex due to the need orientation of the WBT interventions. Depending on the needs of a person, he or she is assigned a different WBT. For example, a person who does not exercise enough and is very overweight is recommended a weight loss WBT, while a person who suffers from high stress levels is recommended a WBT with autogenic training or mindfulness. For this reason, a detailed list of the content covered in the respective apps or WBTs is provided in Table 2 below.

**Table 2 Tab2:** Detailed list of the contents of the various needs-specific app and WBT modifications

Focus	Sub-focus	App				WBT							
		AusGleich	BIG Balance	myCare+	GetRest	Nutrition	Weight loss	Physical Activity	Spine Gymnastics	Mindfulness	Hatha Yoga	Sleep and Stress	Autogenic training
Individualization	Direct biofeedback	x	x	x	x								
	AVEM patterns	x											
	Telephone coaching					x	x	x	x	x	x	x	x
	Vocational setting	x	x	x	x								
	Need orientation					x	x	x	x	x	x	x	x
Stress and relaxation	Problem-focused	x	x	x	x								
	Deep breathing	x	x	x	x					x	x	x	x
	Mindfulness	x	x	x	x					x	x	x	
	Goal setting	x	x	x	x		x	x		x		x	x
	Gratitude journal	x	x	x	x					x	x	x	
	Positive psychology	x	x	x	x					x	x	x	x
	Autogenic training	x	x	x	x					x	x	x	x
	Progressive muscle relaxation	x	x	x	x					x	x		
	Body perception	x	x	x	x					x	x		
	Stress physiology												x
Sleep	Sleep habits	x	x	x	x								
	Sleep and shift work	x	x	x	x								
	Healthy sleep	x	x	x	x							x	
Physical activity	Stretching and yoga	x	x	x	x			x			x		
	Fascia						x	x	x				
	Behavior change	X	x	x	x								
	Activity habits	x	x	x	x								
	Endurance training	x	x	x	x			x					
	Anatomy						x	x	x				
	Spine health								x				

#### Strategies to improve adherence to interventions

In order to improve adherence to interventions, a user-centered approach was chosen to integrate experiences and test the functionality of the app internally and externally. Moreover, the information process about the study design implied an explanatory video, numerous flyers, and digital meetings. After agreeing to participate, numerous reminder emails were also created, which were automatically sent to the participants if they forgot to order the sensors or register.

#### Participant involvement

To ensure target group participation, the intervention conception was preceded by a qualitative needs assessment of the target group health care workers. We inquired about acceptance of the biofeedback system, the chest strap, and needs and requests for app content to improve need-tailoring and individualization aspects. For the sake of simplicity, we do not report the outcomes of this assessment in this study protocol.

### Outcome measures

The assessment will apply a selection of standardized questionnaire measures (cited below) as well as sensor-based physiological and vital parameter measures (measured by Corvolution CM300, which includes ECG circuit, 3-axis acceleration and rotation rate chip, air pressure chip, thoracic impedance chip, and temperature chip). Additionally, demographic characteristics, such as age, gender, and job hierarchy, will be assessed.

#### Primary outcomes

All primary outcomes will be assessed at baseline (*T*
_1_), at follow-up measurement after 8 weeks (*T*
_2_), and at follow-up measurement after 16 weeks (see Table 1).

##### Stress and relaxation

While perceived stress and stress symptoms will be assessed in a questionnaire format, heart rate variability (HRV) and sympathovagal balance are captured by the sensor.□ *HRV*: HRV measurement will be used to determine the ability of the heart to respond to daily physiological and psychological stimuli. The following HRV parameters will be used for the assessment of psychological health and stress: SDNN (ms), RMSSD (ms), LF (ms2), HF (ms2), and the LF / HF-Ratio.□ *Perceived Stress*: Stress perception will be assessed via the PSS-4 questionnaire. The PSS-4 is the short version of the original PSS-10, developed by Cohen et al. [86], which measures the extent to which respondents perceive their life situation as unpredictable, uncontrollable, and overloaded, and thus feel stressed. The 4-item version incorporates the statements: “In the last month how often have you felt you were unable to control the important things in your life?,” “In the last month how often have you felt confident about your ability to handle your personal problems?,” “In the last month how often have you felt that things were going your way?,” “In the last month how often have you felt difficulties were piling up so high that you could not overcome them?”. The 5-point response scale ranges from 0 = never to 4 = very often. Internal consistency is good at *α* = 0.77 [87].□ *Subjective stress symptoms*: A self-developed questionnaire asks respondents to rate 10 stress symptoms (e.g., I often feel alone, abandoned, and isolated) on a 5-point Likert scale (not true—true).

##### Sleep quality

Sleep quality will be measured via both sensor data (sleep duration and sleep recovery) and validated questionnaires (subjective sleep quality, sleep apnea risk).□ *Sleep duration*: Determination of sleep duration follows the method of Cole et al. [88]. Classification of sleep duration occurs as hours/day, where <6 h/day = insufficient, 6–9 h/day = sufficient, and >9 = excessive [89].□ *Sleep recovery*: ECG parasympathetic activation will measure sleep recovery. Via the sensor, participants’ recovery will be classified as poor, moderate, or good.□ *Subjective sleep quality*: The Pittsburgh Sleep Quality Index (PSQI) will be used to collect subjective sleep quality data. The index is composed of 18 items covering seven relevant areas (subjective sleep quality, sleep latency, sleep duration, habitual sleep efficiency, sleep disturbances, use of sleep medications, and dysfunction during the day within the past four weeks) [90]. An example item is “During the past 4 weeks, how often have you slept poorly because you woke up in the middle of bedtime or much too early?” Across the seven areas, a total of 0–21 points can be achieved. Scores above 11 reflect poor sleep quality, whereas a score of 5 and below reflects good sleep quality. The German version demonstrated good internal consistency (*α* = 0.75 [91];).□ *Sleep apnea risk*: The snoring, tiredness during daytime, observed apnea, and high blood pressure with BMI, age, neck circumference, and gender (STOP-Bang) questionnaire will be used to identify obstructive sleep apnea (OSA) risk. The STOP-Bang questionnaire asks four yes/no questions (“Do you snore loudly (louder than talking or loud enough to be heard through closed doors)?”, “Do you often feel tired, fatigued, or sleepy during daytime?”, “Has anyone observed you stop breathing during your sleep?”, “Do you have or are you being treated for high blood pressure?”) to quickly screen OSA risk. Respondents are assigned a score for each item (no = 0, yes = 1) for a possible score of 0 to 8 points. Using a cut-off score ≥ 3, the STOP-Bang questionnaire exhibits high sensitivity to detect any OSA (84%), moderate-to-severe OSA (93%), and severe OSA (100%) [92].

##### Physical activity and fitness

Sensor-based measures of physical activity and fitness measures include daily steps, energy expenditure, activity intensity and variety, physical inactivity, and BMI.□ *Steps*: Accelerometer-based measurement of steps (steps/day) will be recorded, and participants will be categorized as low active (<5000 steps/day), moderately active (5000–10,000 steps/day), and highly active (>10,000 steps/day) adapted from the Tudor-Locke & Bassett [93] framework (originally: sedentary (<5,000 steps/day), low active (5000 to 7499 steps/day), somewhat active (7500 to 9999 steps/day), active (10,000 to 12,499 steps/day), and highly active (>12,500 steps/day)).□ *Total daily energy expenditure*: Based on the work of Livesey [94], daily activity will be computed as the discrepancy from the individual basal metabolic rate (BMR; MJ/day) requirements determined by age, sex, and body weight (kilograms). Participants with total daily energy expenditure <1.5, BMR are considered low active, 1.5–1.7 BMR reflects moderate daily activity, and daily energy expenditure >1.7 BMR will be treated as highly active.□ *Activity variety*: Metabolic equivalent of task (MET) minutes/day will be assessed for daily activities [95].□ *Activity intensity*: Activity intensity will be computed as mean heart rate in relation to minimum and maximum rate during the measurement period.□ *Physical inactivity*: Physical inactivity will be assessed as the number of minutes per days those participants exhibit waking inactivity (sitting, standing) Classification is as follows: <60 min/day = good, 60–240 min/day = moderate, >240 min/day = poor. Also, inactivity disruptions will be measured, operationalized as a disruption of a ≥ 30-min inactivity period for at least 1 min (e.g., short walk after a 30-min sitting period).□ *BMI*: The BMI will be computed (kg/m^2^). According to the WHO [96], participants will be classified as underweight (<18.5 kg/m^2^), normal weight (18.5 to 25 kg/m^2^), and overweight (>25 kg/m^2^). Height and weight are assessed by questionnaire.

#### Secondary outcomes

##### Behavioral and experiential outcomes

In addition to the three primary outcome domains of stress, sleep, and physical activity, information was collected on experienced back pain, health behaviors, work-related behavior and experience patterns, and personality. These were used to tailor the app. All behavioral and experiential secondary outcomes will be assessed at baseline (*T*
_1_), at follow-up measurement after 8 weeks (*T*
_2_), and at follow-up measurement after 16 weeks (see Table 1).□ *Back pain*: The back complaints of the last 7 days are surveyed using three self-developed items, addressing the location and situations in which back complaints occur.□ *Health behavior*: Based on the Health Action Process Approach, 22 items were adapted from Schwarzer [97] to capture motivational and volitional mechanisms that influence individual stress management practices. Items include statements regarding self-efficacy, intentions, outcome expectancies, planning, and actual stress coping behavior (e.g., “How certain are you that you can execute the exercise in the app?”). All items are assessed on a 5-point Likert scale (e.g., 1: not at all certain–5: very certain).□ *Work-related behavioral and experiential patterns*: To assess the Work-related Behavior and Experience Patterns (German acronym AVEM), we included four items that were self-developed based on the 44-item original version by Schaarschmidt & Fischer [98]. The original questionnaire comprises 44 questions covering eleven dimensions (subjective meaning of work, occupational ambition, energy expenditure readiness, perfectionism, emotional distancing ability, resignation tendency, offensive problem coping, internal peace and balance, perceived work success, life satisfaction, and perceived social support). Respondents are clustered into one of four patterns (health, conserving, overexerting, and burnout) that can be used to identify individual intervention targets. The condensed 4-item version used for this study was validated in an online survey (e.g., “My job is important to me, but I also manage to distance myself from my work and thus maintain a high quality of life.”). The internal consistency of the original version ranges from 0.79 to 0.87 [99].□ *Personality*: We will include the Big-Five-Inventory-10 (BFI-10) comprising ten items that economically measures personality based on the five-factor model [100]. The procedure was shown to be reliable in evaluation studies with a retest reliability of 0.49 to 0.84 and exhibited good content as well as convergent validity. An example item of this scale is “I trust others easily, believe in the good in people.”

##### App-related outcomes

During the intervention, usage data was also collected that included information about satisfaction with the app, modules completed, intensity of use, and duration of use. App-related secondary outcomes will only be assessed during the intervention period (see Table 1).□ *Satisfaction with internet-based programs*: To assess the satisfaction with internet-based training, we include the Client Satisfaction Questionnaire-Internet (CSQ-I), which measures the acceptance towards digital interventions with eight items (e.g., “I am satisfied with the amount of help I received from the training”). The questionnaire has very good reliability with *α* = 0.94 [101].□ *App usage data*: Tracking of intervention module finalization and total time spent with allocated modules will be performed.

### Data collection, management, and analysis

Relevant outcome variables will be assessed at three time points. The different measurement points are the same for all five intervention groups. The baseline measurement (*T*
_1_) is first carried out on the participants directly prior to beginning with the interventions. The post-intervention measure will be performed immediately after the interventions are completed (*T*
_2_). After another 6 weeks of no intervention, the sustainability measurement (*T*
_3_) will be conducted. For the waiting control group, the first measurement (*T*
_1_) will be followed by a period of eight weeks of waiting. The second measurement (*T*
_2_) will be conducted after this waiting period. Then participants of the waiting control group will receive one of the interventions and then have their third measurement directly after finishing the respective intervention (*T*
_3_). At all three measurement points, the same variables, namely physiological stress, perceived stress, satisfaction with the digital intervention, personality, work-related behavior patterns, and team conflict will be measured.

The respective measurement tools that will be applied are described in the outcomes section including information on reliability and validity. In order to promote data quality, we include evaluated scales that appeared to be reliable and valid in previous studies. We will not conduct duplicate measurements. The collected data will be processed pseudonymously in digital form (from the initial measurement to the sustainability study—approx. 12 weeks).

In order to ensure pseudonymization and simultaneously ensure subsequent deletion of the data, each participant creates a five-digit individual code word immediately after signing the consent form when answering the initial survey, consisting of the first letter of their mother’s first name, the first letter of their favorite color, the first letter of their place of birth, the last digit of their year of birth, and the last digit of their day of birth (e.g., MGF01). This code is used instead of other identifier in all subsequent measurements. There is a coding list on paper that links the name to the code but is only accessible to the investigators and the project manager. The coding list is kept in a lockable cabinet or safe and is destroyed after the data collection is completed. If a respondent wishes to delete their data retrospectively, they can use the five questions mentioned above to reconstruct their code word and thus request deletion of the data. After completion of the sustainability measurement, the code used to pseudonymize the employees will also be replaced by assigning a combination of numbers (e.g., 1647) and thus anonymized. Non-anonymized data sets are deleted by the university and the cooperation partners involved in the data collection after completion of the data collection. Data will only be processed in anonymized form within the framework of the study and for subsequent scientific use as well as for publication of the study results.

The anonymized data sets will be stored on a password-protected project folder of the TUB cloud of the TU Berlin for the duration of the project until the completion of all scientific work and associated data analyses. Subsequently, the data will be transferred to a research data repository of the TU Berlin and stored there for a period of 10 years. Access to the server is granted by assigning passwords to the external project partners. The rights to assign the passwords lie with the project leader PD [name]. After completion of the project, all raw data collected can be made publicly available in anonymized form in a research data repository for an unlimited period of time as part of the Open Science efforts of the scientific community and in accordance with the Berlin Declaration. Personal information about the participants will be protected by pseudonymization of the data sets described above.

#### Statistical analysis

Primary and secondary outcomes will be analyzed using SPSS software. The study will allow a comparison between all summarized intervention groups with the waiting control group, as well as a comparison between the different intervention groups. Additionally, participation rates will be included in the analyses. Sample characteristics will be explored applying descriptive statistics. Standard analyses adjustments will be made to adjust for baseline differences between groups, in case there are any. For missing data, sensitivity analyses will be conducted to compare results with the complete case analysis. Further, different options for imputation will be considered. Differences between intervention groups and the control group will be investigated using *χ*
^2^ tests for categorical variables and independent sample *t*-tests for continuous variables. General linear mixed models will be applied for the statistical analyses of primary and secondary outcomes. Group-based trajectory modelling will also be applied if feasible given the data situation. The models will be adjusted by baseline value and potential confounders, such as staff field of working (hospital, stationary elderly care, ambulatory care) or age. *P* values <.05 will be considered as statistically significant and effect sizes of >.3 will be regarded as clinically significant. If appropriate, 95% CI will be reported with the *p* values as well. If feasible, missing data will be imputed through multiple imputation.

#### Monitoring

The research team will promote participant retention through close personal support. Contact persons will always be available for any occurring questions or problems. Further regular reminder emails will be sent out as soon as participants appear to fade out of completing the interventions. A respective data monitor will be named and be responsible to supervise the active participation. If there is no response to the reminder emails, participants will be contacted by phone by the research team. If participants decide to withdraw from the intervention, no further data of them will be collected.

All researchers involved in the study will monitor the data and report in case of appearing inconsistencies or other problems. In the beginning of the project, data monitoring will take place on a daily basis. As soon as the study runs smoothly, data will be monitored on a weekly basis.

We do not expect that any adverse effects appear during the study. However, in case any solicited, and spontaneously adverse events are reported, the research team will inform the supervisor and decide based on her expertise how to deal with the events. The investigators will audit the trial conduct on a weekly basis to inspect how the trial is going and whether any adaption or intervention is necessary. This will be done in collaboration with the trial sponsor. In case any protocol amendments will be necessary, the ethical committee that granted approval for the present trial will be informed immediately. Additionally, all participants will be informed about changes. The results of the trial will be reported to participants and their institutions in an anonymized report that is specifically designed to be understandable by people without a scientific background. The study results will further be made available to the public and interested researchers through an open access publication in peer-reviewed journal.

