### Research questions

The main research question of this study is:□ Which digital intervention is most efficient for improving the stress management skills of health care and administrative personnel?

Regarding this main question, there might be some group-related differences to detect. Therefore, the following research questions should be answered:□ What are the differences in stress levels between nursing and administrative health personnel?□ What are the differences in sleep quality between nursing and administrative health personnel?□ How do intervention formats differ with regard to the effects on the processes of behavioral change?

Moreover, there are some outcome-related research questions:□ What is the association between the usage of mHealth intervention applications during working hours and stress levels of users?□ Is the effectiveness of the mHealth interventions determined by the age or gender of the participants?□ Is there a connection between stress and other outcomes such as back pain or physical activity levels?□ Do mHealth interventions contribute to a reduction in back pain?

Finally, the study should answer some acceptance and individualization related research questions:□ What is the rate of acceptance for the sensor-based mHealth interventions for nursing and administrative health personnel?□ What is the level of satisfaction for the sensor-based mHealth interventions for nursing and administrative health personnel?□ Do additional intervention requirements (e.g. for individualization) emerge as a result of the sensor screenings?□ What are the necessary requirements to ensure a long-term integration of sensor-based mHealth interventions to the daily routine of nursing and administrative health personnel?

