**Table 1 Tab1:**
[figure not shown]
Schedule of enrollment, interventions, and assessments: Recommendations for Interventional Trials (SPIRIT) chart of the enrollments and assessments during randomized controlled trials

The five intervention groups are as follows:Web-based digital stress management intervention (WBT only)Web-based and need-oriented digital stress management intervention (WBT + Need)Web-based and need-oriented digital stress management intervention with telephone coaching (WBT + Need + Coaching)App-based stress management interventions with sensory biofeedback (App + Biofeedback)App-based stress management intervention with sensory biofeedback and health report (App + Biofeedback + Report)

All participants of the intervention groups will receive a digital intervention. The waitlist control group will start the intervention after 8 weeks. Both, questionnaire and sensory data will be assessed:At baseline (*T*
_1_: pre-intervention/pre-waiting)At 8 weeks (*T*
_2_: post-intervention/post-waiting=pre-intervention)At 16 weeks (*T*
_3_: sustainability or post-intervention for waiting group; see Table 1).

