### Participants

#### Eligibility and ethical approval

The crossover randomized controlled trial will include nursing staff and office workers aged 18 years or older from hospitals, stationary elderly care facilities, and ambulatory care providers. No clinical patients will be involved in the proposed study. Fluency in the German language as well as internet access via a smartphone device are prerequisites for study participation. All potential participants will be informed about the study and its procedure through a comprehensive informative video. The study is conducted in agreement with the principles of the Declaration of Helsinki and the guidelines of Good Clinical Practice. The recruitment of the participating nursing facilities involved cooperating health insurance companies, whereas the recruitment within the participating facilities will remain within the responsibility of the authors. Written informed consent will be obtained from all participants or their legal guardians before enrolment. Participants as well as their relatives or legal guardians can withdraw consent at any time. The local ethics committee of the TU Berlin, Germany, has approved the study protocol (No GR_14_20191217). The trial was registered at DRKS.de with registration number DRKS00021423 on 12 July 2021.

We used the program G*Power [81] to calculate the relevant sample size. To achieve the sample sizes required by power analysis with a β-error of 80% and an effect size of 0.25, we will need to include 700 participants. An effect size of 0.25 is considered a small effect, which is congruent with the literature on the effectiveness of eHealth/mHealth behavior change interventions [82, 83] and workplace health promotion interventions [84]. We expect a participation rate of 20% as this appeared to be a realistic participation rate in previous intervention studies in different small and middle-sized companies [85]. With an expected dropout rate of 20%, we will include additional 140 participants to ensure that the study results will still be eligible for data analyses.

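### Stopping data collection at withdrawal from the intervention can, before T2, remove outcomes only from the intervention groups and so cause differential missingness against the waiting group

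*Protocol article*

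**What the plan says.** The Monitoring section of the protocol article first deals with participants whose use of the programme is tailing off: they get reminder emails and, if they do not answer, a phone call. It then sets the rule at issue: "If participants decide to withdraw from the intervention, no further data of them will be collected".

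Leaving the study has its own provision, under Eligibility and ethical approval: "Participants as well as their relatives or legal guardians can withdraw consent at any time". No section provides for assessing someone who has withdrawn from the intervention but not from the study.

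On the control arm, the Study design section says: "The waitlist control group will start the intervention after 8 weeks". Data collection, management, and analysis gives the same sequence: T1, eight weeks of waiting, T2, then an intervention, then T3.

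The Statistical analysis section plans "a comparison between all summarized intervention groups with the waiting control group, as well as a comparison between the different intervention groups". It names general linear mixed models adjusted for baseline and potential confounders, sensitivity analyses set against complete cases, and multiple imputation if feasible.

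**The concern.** Stopping a web course or app is something that happens after randomisation and may result from the allocated programme. Someone who stops can still fill in an online questionnaire and apply a sensor. Ending data collection at that point turns a treatment decision into missing outcome data.

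In most parallel designs such a rule acts on every arm. Here, before T2, it cannot act on the waiting group. T2 is also the only randomised contrast with an untreated control, because the waiting group is treated before T3. If those who withdraw differ from those who stay, the intervention groups at T2 are a selected remainder, and this rule selects nobody out of the control group.

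The main research question ("Which digital intervention is most efficient for improving the stress management skills of health care and administrative personnel") is a comparison between interventions. All five groups are open to the rule there, so distortion needs withdrawal that differs by format in rate or in type of person. The Discussion expects individualisation to raise adherence, and increasing adherence is one of the stated aims, so such a difference is plausible. No withdrawal rates by arm are given.

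**Working it through.** **1. Who can trigger the rule, and when.** The protocol has no figure of its own to reproduce here, so the first step sets its sections side by side.

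| Period | Five intervention groups | Waiting group |
|---|---|---|
| T1 to T2 (week 8) | On intervention: rule can apply | No intervention yet: rule cannot apply |
| T2 to T3 (week 16) | Intervention over | On intervention: rule can apply |
| Consent withdrawal or non-response, any time | Possible | Possible |

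The asymmetry before T2 belongs to this rule alone. It does not describe all missing data.

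**2. Why the planned analysis cannot settle it.** A participant who withdraws before T2 contributes T1 only. A mixed model or standard imputation then takes the T2 value from others in the same arm with similar baseline data, all of them people who did not declare withdrawal. Since nobody is measured after declaring withdrawal, the data cannot show whether that assumption is reasonable.

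**3. Illustration of size.** Let q be the share of the intervention groups lost through the rule, and D the gap at T2, in SD units, between stayers and withdrawers that remains after adjustment. The mean of all allocated participants is (1 − q) × stayers + q × withdrawers, so

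bias of a complete-case contrast = stayers − all = q × D.

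Inputs: q = 0.20 takes the 20% overall dropout figure from the sample-size paragraph and assumes that all of it is loss through this rule before T2, with no control loss. q = 0.10 is a lower alternative. The values of D are assumptions; the protocol gives none.

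| q | D = 0.25 | D = 0.50 | D = 0.75 |
|---|---|---|---|
| 0.20 | 0.05 | 0.10 | 0.15 |
| 0.10 | 0.025 | 0.05 | 0.075 |

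The planned effect size is 0.25, with no metric named. If it is a standardised mean difference, the first row equals 0.05/0.25 = 20%, 0.10/0.25 = 40% and 0.15/0.25 = 60% of it.

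**4. Bias against precision.** Take 700 + 140 = 840 randomised, in six equal arms of 140 (an assumption: the article states no ratio), with outcome SD 1. With 20% lost in the five intervention groups, 5 × 112 = 560 remain against 140 controls.

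- Standard error: √(1/140 + 1/560) = 0.0945.
- With no true effect, the two-sided 5% error is Φ(bias/SE − 1.96) + Φ(−bias/SE − 1.96). For a bias of 0.05 this is about 8%; for 0.10, about 19%.
- Power for a difference of 0.25: 77% with no loss (SE √(1/140 + 1/700) = 0.0926) and 75% with this loss.

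Under these assumptions precision hardly changes. The extra 140 participants protect power and do nothing about selection.

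**The case against.** Several stronger readings are tempting, and the protocol article does not support them.

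- **That any stopping or low use ends follow-up.** The Monitoring section separates people who fade out, who are reminded and phoned, from those who decide to withdraw. Only a declared decision triggers the rule. The low adherence to digital programmes described in the Introduction does not by itself remove anyone from assessment.
- **That the controls are fully observed.** Any participant may withdraw consent, and waiting participants may fail to respond.
- **That the trial's main comparison is biased in favour of the intervention.** No single main comparison is named, and the main research question is between interventions. A bias towards the intervention is plausible if withdrawers do worse, but nothing in the article establishes its direction.
- **That T2 exists only for completers.** One sentence might suggest this: "The post-intervention measure will be performed immediately after the interventions are completed". But the Study design and Primary outcomes sections fix T2 at 8 weeks, and the measurement points are said to be the same for all five groups.

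It can also be said that the sentence is shorthand for leaving the study, in a condensed article whose full protocol is available on request. That is possible. The words used still name the intervention, in a paragraph where the term means the programme, so the sentence would need correcting on that reading too.

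Finally, the illustration assigns the whole overall dropout figure to the active arms and ignores control loss. Adjustment for baseline would shrink a crude gap, which is why D is defined as the gap left after adjustment. These points limit how much weight the figures can bear. The data-collection rule and its asymmetry before T2 remain, and no analysis plan can recover outcomes that were not collected.

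**Conclusion.** The point holds in limited form. The protocol ends all data collection at a declared withdrawal from the intervention and does not distinguish this from withdrawal of consent. Before T2 the rule can remove outcomes only from the five intervention groups. It can therefore cause differential missingness in the pooled comparison with the waiting group, and it can distort comparisons between interventions if withdrawal differs by format.

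The size and direction of any bias are unknown. The range of 0.05 to 0.15 SD at 20% loss, or 0.025 to 0.075 SD at 10%, is an illustration. It assumes a complete-case contrast, loss through this rule in the active arms only, and withdrawers 0.25 to 0.75 SD worse after adjustment. It shows that a moderate gap could matter beside a planned effect of 0.25, not that the result will be biased by that amount.

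**What to change.** Replace the sentence in the Monitoring section with: *Participants who stop the intervention remain in the study and are invited to T2 and T3 at the scheduled 8 and 16 weeks; data collection ends only if consent to the study is withdrawn.* Analyse all randomised participants as allocated, using all observed data, and record the date of stopping by arm.

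The cost is some extra questionnaire invitations and sensor mailings. The questionnaires are online, the sensors are self-applied, and reminder emails and phone contact are already in place. The change also needs an amendment, which under the Monitoring section must be notified to the ethics committee and to all participants.

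The Trial status section reports that measurement started in September 2021 and recruitment was completed in March 2022, so some assessments may already be lost. Where T2 or T3 has been missed, report withdrawals by arm and add a sensitivity analysis in which withdrawers do worse than those who stayed, over a stated range of gaps.
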